## Abstract

**Introduction:**

The prevalence of polycystic ovary syndrome (PCOS) is 10–15% in women of reproductive age. Its characteristics are (i) clinical or biochemical hyperandrogenism, (ii) oligomenorrhea or amenorrhea, and (iii) polycystic ovaries on ultrasound. PCOS is associated with lower quality of life, depression, anxiety, diabetes, and cardiovascular disease. Treatment commonly entails oral contraceptive use to lower endogenous androgen levels. Androgen levels and comorbidities may affect sexual function. Previous studies have addressed a limited range of possible contributing factors. We will assess sexual function as well as genital and self-reported sexual arousal in a laboratory setting in women with PCOS compared to an age-matched healthy control group. Modulation by biopsychosocial factors mentioned will be studied.

**Methods:**

This is a multicenter prospective case control study. The study population includes healthy women with and without PCOS, aged 18–40 years, in a stable heterosexual relationship for at least 6 months. Power is calculated at 67 participants in each group. Anticipating a drop out of 10%, 150 participants will be recruited.

**Main outcome measures:**

The main outcomes measured are sexual function using the Female Sexual Function Index, Sexual Desire Inventory, and Female Sexual Distress Scale-Revised; genital sexual arousal measured as vaginal pulse amplitude; and self-reported sexual arousal in response to erotic stimuli in a laboratory setting. The mediators that will be investigated include testosterone, free androgen levels, oral contraceptive use, sensitivity to androgens (using CAG repeat length), body mass index, body image, mental health, and self-esteem.

**Conclusion:**

Strengths of this study are the inclusion of a broad range of biopsychosocial outcome measures including DNA analysis, a healthy control group, and standardized assessment of genital and self-reported sexual arousal in a laboratory setting. With the design of this study we aim to provide an insight into which biopsychosocial factors associated with PCOS are related to sexual function, and how sexual function may be affected by treatment. These new insights may help to improve clinical management of PCOS while improving the quality of life.

**[name], [name], [name], et al. Sexual Function in Women With Polycystic Ovary Syndrome: Design of an Observational Prospective Multicenter Case Control Study. Sex Med 2020;8:718–729.**

## Background

Polycystic ovary syndrome (PCOS) is the most common endocrine disease in women. Its prevalence is estimated to be between 5% and 15%^1^ in women of reproductive age. Its characteristics are (i) either clinical (hirsutism) or biochemical hyperandrogenism (elevated androgen serum levels), (ii) oligomenorrhea or amenorrhea, and (iii) polycystic ovaries on ultrasound.^2^ Following the Rotterdam criteria, PCOS is diagnosed when 2 out of 3 characteristics are present.^2^ Treatment of PCOS is complex and varies depending on symptoms and whether there is a desire to have children. In the latter group, the first-line treatment in women who are overweight or obese is lifestyle modification followed by ovulation induction. Lifestyle changes contribute to optimizing success rates in establishing a pregnancy and reducing complication rates by normalizing insulin resistance and consequently androgen levels.^3^, ^4^, ^5^, ^6^ In women who do not want to become pregnant, treatment usually consists of oral contraceptive pill (OCP) use and lifestyle changes if indicated.^7^ Both interventions aim at improving endocrine disturbances by normalizing insulin resistance and androgen metabolism. Similarly, OCPs increase SHBG levels and hence reduce free androgen levels.

PCOS is a distressing disease with symptoms such as subfertility, hirsutism, and acne.^7^, ^8^, ^9^, ^10^ It is associated with obesity, insulin resistance, and unfavorable lipid profiles.^7^^,^^9^ Also, PCOS is associated with lower quality of life, depression, and anxiety.^7^^,^^11^, ^12^, ^13^, ^14^, ^15^, ^16^ The most recently published evidence-based guideline on PCOS mentions reduced health-related quality of life scores for women with PCOS compared to a control population.^17^ Health-related quality of life is influenced by the clinical features of PCOS (mainly hirsutism, menstruation, and fertility) and affected by anxiety, poor body image, low self-esteem, depressive symptoms, delayed diagnosis, and inadequate education about PCOS. The guideline also reports a 3 times higher prevalence of depression^15^^,^^18^, ^19^, ^20^, ^21^, ^22^ and a 5-fold increase in the incidence of anxiety disorders^15^^,^^18^, ^19^, ^20^, ^21^, ^22^, ^23^, ^24^ in women with PCOS. Also, body image seems to be impaired in women with PCOS compared to a control population.^25^ Although there is conflicting evidence, hirsutism,^26^, ^27^, ^28^ increased weight,^27^^,^^28^ and infertility^26^ seem to affect body image negatively. A negative body image is strongly associated with depression.^27^^,^^29^^,^^30^ Finally, disordered eating, eating disorders (mainly bulimia nervosa), and risk factors for eating disorders seem to be more prevalent in women with PCOS.^19^^,^^31^, ^32^, ^33^ Psychosocial factors such as anxiety, depression,^34^^,^^35^ poor body image,^36^ and eating disorders^37^ are recognized as potential risk factors for sexual dysfunction and impaired sexual satisfaction.

Data on sexual function in women with PCOS are limited. A systematic review on PCOS and sexual function by our research group compared 18 studies in a meta-analysis.^38^ Sexual dysfunction appeared to be more prevalent in women with PCOS than in the control group. Particularly, sexual arousal, lubrication, orgasm, and satisfaction were compromised. Effect sizes were small for the first 3 aspects of sexual function; for satisfaction the effect size was large. In addition, women with PCOS have fewer sexual thoughts, report self-perceived impaired attractiveness, and report more problems participating in social meetings due to bodily appearance than women without PCOS. Also, women with PCOS report a negative impact of excessive body hair on sexual function. For these variables effect sizes were large, with the exception of number of sexual thoughts which showed a medium effect size. Although women with PCOS were less satisfied with their sex life, having a satisfying sex life was as important to them as it was for control women. In the studies assessed in this meta-analysis, sexual function was mainly studied using questionnaires. Sample sizes were too small to make subgroup comparisons to determine associations between sexual function and weight, hirsutism, mental health, body image, menstrual cycle, endocrine features, or use of OCPs.

It is known that sexual function is influenced by biological,^39^, ^40^, ^41^, ^42^, ^43^, ^44^, ^45^, ^46^ psychological,^34^, ^35^, ^36^^,^^47^, ^48^, ^49^ and social factors.^50^^,^^51^ As mentioned, in women with PCOS all these factors might be compromised,^17^ potentially leading to compromised sexual function.

Sex steroid hormones, in particular estrogens and androgens, play an important role in sexual function,^52^, ^53^, ^54^, ^55^, ^56^ although the exact mechanisms by which these steroids exert their influence are still unclear.^52^^,^^55^, ^56^, ^57^, ^58^, ^59^ Androgens are believed to sensitize the brain and genitals to sexual stimuli.^53^^,^^55^^,^^60^ Estrogens seem to improve sexual function indirectly by improving vaginal health and mood.^55^^,^^57^ Reduced levels of estrogens and androgens are associated with alterations in genital tissue structure and innervation, as well as with response to physiological modulators like neuropeptides and neurotransmitters.^61^ Furthermore, estrogen and androgen deficiencies are associated with reduced expression of sex steroid receptors and most importantly with attenuated genital blood flow and lubrication in response to pelvic nerve stimulation.^61^

An important feature of PCOS is the alteration in sex steroid hormones. In PCOS androgen levels are often elevated, leading to biochemical and/or clinical hyperandrogenism. However, women with PCOS do not report a higher level of sexual desire compared to women without PCOS.^38^ In general, the relationship between androgen levels and sexual desire in women is inconclusive.^57^ Partly, this may be due to the fact that many studies have assumed that androgens and sexual outcomes are linearly and cross-sectionally related across the total serum testosterone or free testosterone range. It is possible though that, as in men,^62^^,^^63^ androgen-related sexual problems in women should only be expected when androgen levels are below a certain hypophysiological threshold. Even less is known about sexual function in women who have androgen levels at the high end of the normal range or who have hyperphysiological androgen levels. In women, findings of a number of studies suggest a threshold approach might be more suitable.^64^, ^65^, ^66^, ^67^, ^68^, ^69^, ^70^, ^71^ This research project aims to contribute to this discussion.

Differences in androgen receptor (AR) activity and hence sensitivity to androgens might complicate the relationship between androgens and sexual function. Functional studies have demonstrated that an inverse relationship exists between the CAG repeat length and receptor expression impacting on the strength of the androgen action and sensitivity to sex hormones.^72^ Several authors have studied the potential association between shorter CAG repeats and a high testosterone level in PCOS as well as the general population, with conflicting results.^73^, ^74^, ^75^, ^76^, ^77^, ^78^, ^79^ Ethnicity, small sample sizes, and different definitions of PCOS and hyperandrogenism may underlie these inconsistent results. Moreover, a non-linear relationship between CAG length and AR activity has been suggested.^80^ Therefore, it is plausible that CAG repeat length variants are involved in the pathogenesis of women with hyperandrogenism and influence sexual function. For instance, a recent Danish population study showed that lower numbers of CAG repeats were associated with problems in reaching orgasm.^81^

The impact of OCP use on endocrine and sexual function has been studied extensively in healthy women.^82^, ^83^, ^84^, ^85^, ^86^, ^87^, ^88^, ^89^, ^90^, ^91^, ^92^ OCPs are known to decrease androgen and free testosterone levels.^56^^,^^57^^,^^90^^,^^92^ Hypothetically, sexual function can be influenced by this mechanism. Repeatedly, studies have shown that some women report an OCP-related improvement in sexual function, some a deterioration, whereas many report no change in sexual function.^82^, ^83^, ^84^, ^85^, ^86^^,^^88^^,^^89^^,^^93^ In women with PCOS, OCPs can restore androgen levels to normal, improving clinical symptoms like acne and to a lesser extent hirsutism.^7^ Few studies have assessed its influence on sexual function. Results varied from improvement of sexual function, while normalizing androgen levels,^94^ to deterioration of sexual desire.^95^

In addition to differences in androgen sensitivity, in women with PCOS neuronal circuits in the brain might be impaired due to hyperandrogenism, resulting in a disruption of sex steroid feedback mechanisms.^96^^,^^97^ Following this line of reasoning, we will assess androgen levels, CAG repeat length, and actual genital response to sexual stimuli (vibrotactile, film fantasy) in a psychophysiological laboratory setting while taking into account the other factors presented here. As a result, we hope to be able to shed more light on the role of androgen levels in sexual responsiveness of women with PCOS.

Women with PCOS report significantly less sexual arousal and lubrication compared to normal controls,^38^ but it is unknown whether women with PCOS actually show abnormal physiological sexual responses. A pilot study concerning the effect of circulating androgen levels found no significant differences in clitoral vascularization in non-aroused women with PCOS in comparison with control women,^98^ but nothing is known about the genital response to sexual stimulation. There are indications that androgens influence sexual response to sexual fantasies and genital tactile stimulation, whereas the effect of visual stimuli is less influenced by androgen levels.^99^^,^^100^ To objectively assess genital response to sexual stimuli and its contribution to sexual function, psychophysiological measurements with vaginal pulse amplitude (VPA) are required.

The primary aim of this study is to assess differences between women with PCOS and control women in the following sexual outcome measures: Female Sexual Function Index (FSFI), Female Sexual Distress Scale-Revised (FSDS-R), Sexual Desire Inventory (SDI), and genital and subjective sexual responsiveness to sexual stimuli measured with VPA. Secondary aims are to investigate differences in these outcome measures between OCP users and non-users in interaction with PCOS status in an exploratory way, and to assess factors that may mediate the relationship between PCOS status and sexual outcome measures.

We will assess the following mediators: testosterone, free androgen levels, OCP use, sensitivity to androgens (using CAG repeat length), body mass index (BMI), body image, mental health, and self-esteem.

We expect to find lower sexual function and higher sexual distress in the PCOS group compared with the control group.^38^ Further, we expect to find stronger genital and self-reported sexual responsiveness in women with higher androgen levels in both the fantasy and vibrotactile stimulation conditions but not with visual sexual stimuli.^99^^,^^100^

Following the threshold model,^64^, ^65^, ^66^, ^67^, ^68^, ^69^, ^70^, ^71^ we do not predict a linear relationship between VPA response and androgen levels (free testosterone and total testosterone). We do expect women with the lowest bioavailable androgen levels (control women using OCPs) to show lower levels of VPA response than women in the upper 3 quartiles of bioavailable androgen levels (women with PCOS not using OCPs).

We hypothesize that women with PCOS will score lower on various psychosocial and mental health measures compared with control women.^17^ We expect these scores to be associated with impaired scores on sexual function questionnaires.^34^, ^35^, ^36^, ^37^

We have no specific expectation for the relationship between sexual outcomes and CAG repeat length in both women with and without PCOS. CAG repeat length will be measured to exploratively assess individual differences in sensitivity to androgens and the relationship with PCOS status and other variables.

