## Methods

### Design

This study is a non-randomized observational prospective case control study in a multicenter setting assessing the difference in sexual function between women with and without PCOS. Additionally, we examine the effect of OCP use resulting in a 2×2 design. The duration of the study will be 4 years. 3 Dutch academic medical centers will participate in this study: Erasmus Medical Center Rotterdam, Leiden University Medical Center (LUMC), and Amsterdam University Medical Center (AMC). Independent variables are PCOS status and OCP use. The dependent variables are sexual function as assessed with questionnaires and genital and self-reported sexual arousal in a laboratory setting.

Ethical approval was awarded by the Ethics Committee of Erasmus Medical Center, Rotterdam, The Netherlands (MEC 2016-216, NL55484.078.16). Local ethical approval was awarded by the Ethics Committees of LUMC (P16.299) and AMC (2016_182/NL55484.078.16).

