### Participant Recruitment and Selection

Women who have been diagnosed with PCOS at the outpatient clinic of the Erasmus University Medical Center will be asked to participate in this study. Also, Dutch patient societies will be requested to advertise for our study. PCOS will be diagnosed according to the Rotterdam criteria.

An age-matched control group of healthy women will be recruited through advertisements in local newspapers, social media, or flyers at the outpatient gynecological clinics of Erasmus University Medical Center, LUMC, and AMC. Control women will also be recruited through the pool of volunteers available at LUMC. In the control group, women with PCOS will be excluded. In case PCOS is diagnosed, data will be used in the PCOS arm.

Inclusion criteria for participation are healthy women with a diagnosis of PCOS, healthy women without another diagnosis concerning the menstrual cycle, women aged between 18 and 40 years, and those with a stable heterosexual relationship for at least 6 months. Due to the nature of the erotic film material and the sexuality questionnaires, only heterosexual women are eligible.

Medical screening involves endocrine screening, assessment of BMI, a menstrual cycle history, a modified Ferriman-Gallwey score, and a transvaginal ultrasound in order to assess the ovarian morphology, antral follicle counts, and ovarian volumes of both ovaries. Total endometrial thickness will also be recorded as well as uterine sizes. The diagnosis of PCOS or of a normal menstrual cycle will be made after a standardized initial examination is performed between 07:45 and 10:00 am after an overnight fast in the early follicular phase of the menstrual cycle (third to fifth day of menses when no hormonal contraception is used) in case of a regular menstrual cycle. In case of a cycle irregularity, the examination will be performed on a random cycle day. In case of OCP use, screening will be on the eighth day of a new cycle after 7 days of not using OCPs. Endocrine features combined with medical screening will determine the diagnosis.

We will recruit women with PCOS and healthy women both either not using hormonal contraceptives (for at least 3 months prior to the start of their participation in this research project) or using OCPs for at least 3 months. We aim to include a similar number of women using OCPs as women not on OCPs in both the PCOS group and the control group.

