Some variables will be used as moderators (Table 1) as they are not caused by the independent variable (PCOS status): a history of sexual and physical abuse measured with Sexual and Physical Abuse Questionnaire (7 items, yes/no answers)^112^; sexual excitation and sexual inhibition propensity by Sexual Excitation/Sexual Inhibition Inventory for Women (36 items, 2 subscales, low Sexual Excitation Scale indicates low excitation, high Sexual Inhibition Scale indicates high inhibition)^113^; relationship satisfaction by Revised Dyadic Adjustment Scale total score (14 items, cutoff >48 for no distress).^114^^,^^115^

All questionnaires have been validated and will be available in a secure online environment.

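### OCP use and CAG repeat length are listed as mediators of PCOS status, which conflicts with the roles the rest of the protocol gives them

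*Protocol article*

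**What the plan says.** **Mediator lists.** One secondary aim in the Background is "to assess factors that may mediate the relationship between PCOS status and sexual outcome measures". The sentence that follows the aims reads "We will assess the following mediators: testosterone, free androgen levels, OCP use, sensitivity to androgens (using CAG repeat length", and then adds BMI, body image, mental health and self-esteem. The abstract, under Main outcome measures, has the same list: "The mediators that will be investigated include testosterone, free androgen levels, oral contraceptive use, sensitivity to androgens (using CAG repeat length".

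**OCP use elsewhere.** Methods, Design: "Independent variables are PCOS status and OCP use", as the two factors of a 2×2 layout. Table 1 also lists OCP use as an independent variable. Participant Recruitment and Selection: "We aim to include a similar number of women using OCPs as women not on OCPs in both the PCOS group and the control group". Statistical Analysis adds OCP use and its interactions to the regression models. It then describes mediation by steroid hormones and by sexual and psychosocial measures, with PCOS and OCP use together on the exposure side.

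**CAG length elsewhere.** Blood Samples and Endocrine Screening measures it from genomic DNA. The Background says "it is plausible that CAG repeat length variants are involved in the pathogenesis of women with hyperandrogenism" and, in the same sentence, that these variants influence sexual function. Statistical Analysis uses CAG length as a predictor in a separate curve estimation and does not name it in the mediation sentence.

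**The protocol's own rule.** Questionnaires: "Some variables will be used as moderators (Table 1) as they are not caused by the independent variable (PCOS status".

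**The concern.** A mediator lies on a path from exposure to outcome, so the exposure must be able to change it. Neither variable meets that condition here, for different reasons.

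The Background says OCPs are the usual treatment for women with PCOS who do not want pregnancy. A real link from PCOS to OCP use is therefore plausible in the population. Recruiting users and non-users in similar numbers within each group takes most of that link out of the sample. A finding of no mediation by OCP use would then be a consequence of the sampling, and could be misread as a fact about PCOS and its treatment.

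An inherited repeat length precedes PCOS. If it is related to both PCOS and sexual function, as the Background considers plausible, it is a common cause. A mediation model would report that association as an effect of PCOS carried through CAG.

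The lists also leave the analyst with roles that cannot all be followed: OCP use is a mediator in two places and an independent variable or exposure in three.

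**Working it through.** **1. The plan's own figure.** The protocol gives no figure for mediation. Its only computed figure is the sample size. A two-sample t-test with d = 0.60, two-sided alpha 0.05/5 = 0.01 and power 0.80 needs 66.6, so 67 per group and 134 in all. With 10% dropout, 134/0.90 = 148.9, so 149 against the stated 150. The figure reproduces, and nothing below changes it.

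**2. OCP use.** With a binary mediator the product-of-coefficients indirect effect is

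indirect = a × b, where a = P(OCP | PCOS) − P(OCP | control)

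and b is the OCP effect on the outcome given PCOS status. The protocol gives no b; −0.5 SD is assumed.

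| Users, PCOS / control | a | a × b |
|---|---|---|
| 50% / 50% (aim met) | 0 | 0 |
| 55% / 45% (drift) | 0.10 | −0.05 SD |
| 60% / 40% (drift) | 0.20 | −0.10 SD |
| 50% / 30% (assumed population, free sampling) | 0.20 | −0.10 SD |
| 70% / 30% (assumed population, free sampling) | 0.40 | −0.20 SD |

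Simulation at 67 per group agrees. Free sampling from the last two rows gives mean indirect effects of −0.10 and −0.20 SD. With 34 users and 33 non-users in each group the indirect effect is zero whatever the population shares. Two rows give the same −0.10 SD, one from recruitment drift and one from a real population difference. The sample cannot tell them apart.

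**3. CAG length.** Assume that PCOS affects nothing, that CAG influences both PCOS liability (correlation r) and the outcome (b = 0.3 SD per SD of CAG), and that cases are the top 10% of liability. Mean liability is 0.1755/0.10 = 1.755 in cases and −0.1755/0.90 = −0.195 in controls, where 0.1755 is the normal density at the 90th percentile. The difference is 1.950, so a = 1.950 × r.

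| r | a | a × b | Simulated a × b | Simulated crude group difference |
|---|---|---|---|---|
| 0 | 0 | 0 | 0.00 | −0.01 |
| −0.1 | −0.195 | −0.06 | −0.06 | −0.06 |
| −0.2 | −0.390 | −0.12 | −0.12 | −0.13 |
| −0.3 | −0.585 | −0.18 | −0.18 | −0.19 |

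In theory the last two columns are equal, because all of the crude difference comes from CAG. The mediation output would look like almost complete mediation although PCOS does nothing. With weaker inputs (a group difference of 0.2 SD in CAG and a slope of 0.2) the product is 0.2 × 0.2 = 0.04 SD.

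**4. The protocol's rule applied.** Questionnaires makes a variable a moderator when PCOS status does not cause it. Genotype precedes PCOS, so CAG length falls under that rule. One of the four planned CAG measures is weighted by X-inactivation and so is not purely inherited, but the protocol nowhere suggests that PCOS alters it.

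**The case against.** The strongest reply is that Statistical Analysis does not clearly run either mediation model. It puts OCP use on the exposure side, already includes the PCOS-by-OCP interaction, and sends CAG length to a separate exploratory curve estimation. Table 1 has neither variable in its mediator rows. This stands, and it limits the harm: the mislabelling rests on one sentence in the abstract and one in the Background. It does not remove the contradiction, because those sentences set out how a stated secondary aim is to be met. Table 1 is weaker evidence for CAG than it looks. Its mediator rows hold only questionnaires and also omit testosterone and BMI, which the Background does name as mediators.

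Three stronger readings are tempting, and the protocol does not support them:

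- A reader might infer that quotas fix the PCOS-to-OCP link at exactly zero. The text states an aim, with no quota or cap, so the link is targeted near zero.
- A reader might infer that a CAG artefact is certain. It arises only if CAG and PCOS are associated, and the Background calls the evidence on CAG and testosterone conflicting.
- A reader might fault the curve estimation for showing no PCOS term. That is one condensed sentence about an exploratory model, and the full protocol or analysis plan may well supply the term.

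**Conclusion.** The two mediator lists contradict the rest of the protocol and should be corrected. An indirect effect through OCP use would be uninformative about PCOS: zero if the recruitment aim is met, and mainly a measure of recruitment drift otherwise (−0.05 to −0.10 SD in the examples). A CAG mediation product would be about zero if CAG and PCOS are unrelated. If they are related, it would label non-causal association as an effect of PCOS (0.04 to 0.18 SD in absolute size under the inputs tried).

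Every OCP share other than the recruitment aim, and every effect size and correlation used for mediation, is an assumption; the protocol gives none. The conclusion about roles does not depend on them. The problem is confined to a secondary aim, and the CAG work is declared exploratory. The primary comparison, the alpha level and the sample size are unaffected, so this is a correction worth making and not a threat to the main result.

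**What to change.** 1. Remove OCP use and CAG repeat length from the mediator lists in the abstract (Main outcome measures) and the Background.
2. Keep OCP use as the second design factor with its PCOS interaction, as Statistical Analysis already has it.
3. State that mediation through androgens is estimated conditional on OCP use, since the Background says OCPs lower androgen and free testosterone levels.
4. Assign CAG length the role of moderator (for example an androgen-by-CAG term) or of pre-exposure covariate.
5. Make Table 1 and Statistical Analysis show the same roles.

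The cost is wording and a slightly shorter set of mediation models. No new data or participants are needed.

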### Statistical Analysis

Normality of the outcome data will be determined with Shapiro-Wilk tests. In case of non-normality, an appropriate transformation will be performed. The difference between women with PCOS and controls will be analyzed with separate multilevel regression analyses for each of the 5 outcomes. Independent variables will be PCOS (vs controls), fantasy (vs film), and vibration and interactions of PCOS with fantasy and vibration. *P* values of .01 will be considered significant.

For the differences between women with PCOS and controls, and women using OCPs and women not using OCPs, OCP use and interactions with PCOS, fantasy, and vibration will be added to the multilevel analyses.

Mediation regression analyses, as described by Mathieu and Tailor,^129^ will be extended to multilevel mediation regression analyses to estimate the mediating effects of steroid hormone levels, and sexual and psychosocial parameters in the relation of PCOS/OCP use on the 5 sexual outcome measures.

We will apply regression curve estimation with sexual function as the dependent variable and CAG repeat length and several functions of the CAG repeat length as independent variables to analyze a possible non-linear relation.

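### The androgen threshold hypothesis treats one cell of the 2×2 design as the upper three quartiles, and no stated analysis of measured androgens can test a threshold in VPA response

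*Protocol article*

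**What the plan says.** In the Background section, the hypothesis paragraph on the threshold model says "we do not predict a linear relationship between VPA response and androgen levels (free testosterone and total testosterone"). It then sets out the comparison. On the low side are "women with the lowest bioavailable androgen levels (control women using OCPs"). On the high side are "women in the upper 3 quartiles of bioavailable androgen levels (women with PCOS not using OCPs").

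The Design section says "we examine the effect of OCP use resulting in a 2×2 design", the factors being PCOS status and OCP use. Participant Recruitment and Selection adds: "We aim to include a similar number of women using OCPs as women not on OCPs in both the PCOS group and the control group".

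In the Statistical Analysis section, measured hormones appear once, in multilevel mediation regression "to estimate the mediating effects of steroid hormone levels" and other parameters. A non-linear analysis is named once, as "regression curve estimation with sexual function as the dependent variable and CAG repeat length" and functions of it as predictors. A separate step adds OCP use, and its interactions with PCOS and the stimulus terms, to the multilevel models for the five outcomes.

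**The concern.** There are two linked problems.

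- **The definition.** The quartile wording and the bracketed labels describe different women. An analyst could follow either and would run a different test on a different subset.
- **The analysis.** Earlier in the Background, the authors suggest that past findings may be inconclusive partly because linear relations were assumed, and they offer this project as a contribution to that debate. Yet the variable with a predicted non-linear effect (androgens) has no non-linear or quartile term. The variable with no prediction (CAG repeat length) has one, and its outcome is sexual function, not VPA.

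At stake is whether the study can say anything about a threshold. If the cell contrast is reported as the test, a lower VPA response in control OCP users could be read as support for the threshold model when a linear androgen effect, PCOS itself or OCP use itself would produce the same result.

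**Working it through.** **Inputs from the protocol.** Two-sided alpha 0.01, power 0.80, 134 evaluable women, and a VPA benchmark of d = 0.66 (Sample Size Calculation); four cells of similar size (Design; Participant Recruitment and Selection).

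**1. The plan's own figure.** For SDI, d = 0.60: n = 2(2.576 + 0.842)²/0.60² ≈ 65 per group by the normal approximation, and 66.6, so 67, by the two-sample t-test. The stated 67 per group (134 in total) reproduces.

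**2. Cell against quartiles**, assuming equal cells and whole-sample quartiles:
- PCOS without OCP: 134/4 = 33.5 women (25%).
- Upper three quartiles: 134 × 3/4 = 100.5 women (75%).
- The cell can be at most 33.5/100.5 = one third of the group it is said to represent.
- PCOS OCP users and control non-users, 67 of 134, are on neither side of the bracketed comparison.

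**3. What the planned model can deliver.** Code PCOS and OCP use as 0/1, with control non-users as reference. The mean is b0 + bP for PCOS non-users and b0 + bO for control OCP users. The bracketed contrast is therefore bP − bO: the PCOS effect in non-users minus the OCP effect in controls. It is estimable, but no measured androgen enters it and both factors change at once.

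**4. Does its sign separate the two models?** An illustrative simulation used 33 women per cell and assumed androgen means of −1.2 (control OCP), −0.4 (PCOS OCP), 0.3 (control non-user) and 1.3 (PCOS non-user), with residual SD 0.6. The average contrast was:
- 0.49 when the truth was a 0.66 SD step at the 25th percentile;
- 0.66 when the truth was a straight line with slope 0.66/2.5.

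The standard error was about 0.25 in each case. Both are positive and they differ by less than one standard error.

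**5. Power at d = 0.66, alpha 0.01** (t-test, one VPA value per woman):

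| Contrast | Noncentrality | Power | Detectable d at 80% |
|---|---|---|---|
| Cell vs cell, 33 vs 33 | 0.66 × √(33×33/66) = 2.68 | 0.51 | 0.86 |
| Lowest quartile vs upper three, 33 vs 99 | 0.66 × √(33×99/132) = 3.28 | 0.75 | just under 0.70 |

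At alpha 0.05 the powers are 0.75 and 0.90. The cell contrast would need 55 to 56 women per cell for 80% power at alpha 0.01.

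**6. Illustrative power by androgen coding.** Assumptions: N = 134; log androgen shifted +0.8 by PCOS and −1.2 by OCP; residual SD 0.6; VPA lower by 0.8 SD in the lowest quartile only; alpha 0.01; 4,000 runs. Small differences in set-up move the results by up to about three points.

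| Androgen term | Unadjusted | Adjusted for PCOS and OCP |
|---|---|---|
| Quartile indicator | about 91% | about 71% |
| Linear in log androgen | about 61% | about 19% |

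The step sits exactly at the quartile cut, so the quartile indicator is favoured by construction. In this set-up control OCP users made up about 70% of the lowest quartile, so cell and quartile differ at the low end too.

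**The case against.** **The prediction can be read as directional and is estimable.** On this reading the brackets name the groups in which low and high levels are expected, and the predicted ordering of those two cells follows from the planned PCOS, OCP and interaction terms. This stands. A reader might infer that the plan does not test its prediction at all; that goes too far. What the plan lacks is a test of the threshold, because the cell contrast cannot distinguish a threshold from a line.

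**Linearity of the mediation paths is not stated.** A reader might infer that androgens are to be tested in the very form the authors reject. The article says only that the mediation is multilevel and does not give the functional form. That detail may sit in a fuller analysis plan, so its absence is not held against the article here. The point that remains is an imbalance within the article itself: it assigns the non-linear analysis to CAG repeat length and not to androgens.

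**The reference population for the quartiles is not given**, and similar cell sizes are only an aim. This stands as a limit on the 25% versus 75% arithmetic. If the quartiles were meant within some other group, the text would be ambiguous instead of contradictory, and would still need clarifying.

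**The simulated powers rest on invented inputs.** This also stands. In particular, setting an untransformed linear term (18 to 19%) beside an unadjusted quartile test (91 to 92%) would exaggerate the gap. The fair comparisons are those within each column of the second table.

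**Conclusion.** The point holds in limited form. As written, the threshold hypothesis equates about a quarter of the sample with three quarters of it, given similar cell sizes and pooled quartiles, and leaves about half the women unassigned. The stated analysis contains no threshold, quartile or curve term for measured androgens on VPA. The one comparison that can be derived mixes androgen level with PCOS status and OCP use, does not discriminate between a threshold and a linear relation, and has about 51% power at the protocol's VPA benchmark. That benchmark comes from premenopausal versus postmenopausal women, so applying it here is an assumption.

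This concerns a named hypothesis, but not the primary PCOS-versus-control comparison or the sample size. It should be corrected before the androgen results are analysed.

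**What to change.** - Drop the bracketed cell labels from the hypothesis. Define the groups on measured androgens, as the lowest quartile of the pooled sample against the upper three, and state that the quartiles are pooled.
- Do this for total testosterone and for the free androgen index. The hypothesis names total and free testosterone, and the blood-sample section provides total testosterone and the free androgen index.
- Test this term on VPA response in the multilevel model across the stimulus conditions. Report it with and without adjustment for PCOS status and OCP use.
- As sensitivity analysis, fit a restricted spline of the log androgen measure.
- If the control-OCP versus PCOS-non-OCP contrast is kept, describe it as a group comparison and not as evidence for a threshold.

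**Cost.** The change is to wording and analysis only. The androgens are already to be measured in all participants, so no new data are needed, although the article describes recruitment as ongoing. A quartile cut loses information if the relation is in fact linear, which the spline covers. Adjustment for PCOS and OCP use lowers power, illustratively from about 91% to 71% for an assumed 0.8 SD step. The unadjusted estimate keeps that power but remains open to confounding by both factors, so both should be shown.
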